### Allocation concealment mechanism

The generated sequence will be distributed in numbered sequentially opaque sealed envelopes, which should be opened by the dental assistant immediately before of the restorative procedure, after selective caries removal.

### Treatment procedures

#### HVGIC restoration

In experimental group, after prophylaxis and relative isolation, selective dentin caries removal will be conducted, removing infected dentin from the pulp wall and with total removal of the surrounding walls, using curettes compatible with cavity size. Afterwards, the preconditioning of the surface with polyacrylic acid for 10 s will be performed, followed by washing and drying of the cavity. HIVGIC (Fuji IX; GC Corporation, Tokyo, JP) will be mixed according to manufacturer’s instructions, inserted into the cavity with the aid of an insertion spatula and adapted by the finger press technique. In occlusoproximal cavities, metal matrix will be used to ensure the contact area between the restored and adjacent teeth. The occlusion will be then checked with carbon paper and, if necessary, occlusal adjustment will be performed. Superficial protection of the restoration with petroleum jelly will be conducted.

#### Restoration with hydroxide calcium cement associated with HVGIC

In control group, after prophylaxis and relative isolation, selective dentin caries removal will be conducted in according with experimental group, and then a pulp capping material (Hydro C; Sirona, Pennsylvania, USA) will be applied as liner on pulp wall. After, the restoration with HVGIC will be performed as previously mentioned for experimental group.

The other teeth identified with caries lesions that will be not included in the study will be treated according to the diagnosis by participants of CEPECO collaborative group (Fig. 2).

**Fig. 2 Fig2:**
[figure not shown]
Organization chart of decision-making process of teeth not included in the trial

Furthermore, all participants and their respective legal guardians will receive hygiene and diet instructions. The risks for the participants of this study are minimal and related to the conventional treatment for deep caries lesion. There is no data monitoring committee.

### Data collection and outcomes

Confidentiality of participants will be ensured by an identifier number. Data will be stored in a password-protected electronic database by one of investigators, which only will be available to the researchers. Another investigator will go then double-checking of entered data.

The primary outcome will be the success rates of pulp vitality for both groups after follow-up for 2 years. Secondary outcomes will include survival of restorations, caries progression, self-reported discomfort and cost-efficacy of both types of restorative treatment.

Two blinded examiners will be trained to outcomes assessment. The training will be performed in two phases:Theories classes with images during 3 h.Clinical phase with children with similar conditions to be considered in trial, but not included, during 20 h.

#### Primary outcome

##### Pulp vitality

Pulp vitality will be evaluated after 6, 12, 18 and 24 months through clinical examination using PUFA index [15] linked to radiographic analysis. It will be considered success when minor failures will be observed (failures which could be resolved by replacing or repair of failed restoration). Failure of treatment will be pondered in the presence of major failures as visible pulp involvement, ulceration, fistula and abscess. Reported pain and pathological mobility will also be contemplated. Moreover, we will be considered major failure when the teeth will present radiographically visible furca/periapical lesion.

#### Secondary outcome

##### Survival of restorations

Survival of restorations will be evaluated after 6, 12, 18 and 24 months through of new clinical examination using the criteria by Frencken et al. [14] to occlusal cavities and that proposed by Roeleveld et al. [18] for occlusal-proximal restorations. In occlusal restorations those that receive 0, 1 or 7 score will be considered as success, whilst for occlusoproximal cavities it will be considered as success only those that show 00 or 10 scores. In failures cases, it will be registered the number of surfaces involved in the caries progression and the repair of restoration will be performed.

##### Caries progression

For the evaluation of the caries progression, the bitewing radiographic examination will be used. Radiographic shots will follow the protocol: it will be used a children’s E-speed film (E-speed, 22x35mm, Eastmam Kodak, Rochester, USA), with 0.4 s of exposure, apparatus with Spectro 70X. All radiographs will be made with positioners (Jon Han-Shin PF 682, Jon Ind., Sao Paulo, BRA), apron and lead collar. The films will be processed in boxes of manual processing by the time / temperature method (temperature around 27 °C, developer solution for 2 min, fixer solution for 10 min, washing in water for 20 min). Three radiographs per patient will be performed (1. At the initial exam, 2. After the restorative procedure, 3. Follow-up after 24 months). Initially, two examiners previously trained and calibrated by a reference examiner will evaluate the radiographs independently. The follow ups radiograph will then be compared with post-operative radiograph in order to assess a possible caries lesion progression:A)No progression: when there is no increase in the radiolucent area of the lesion.B)Present progression: when there is an increase in the radiolucent area of the lesion.

##### Self-reported discomfort

The child will also be questioned about the discomfort in relation to the treatment performed. For this purpose, the Wong-Baker face scale [19] will be used. This will be showed by the dental assistant, without the presence of the operator, immediately after treatment, and the child will point to the image which represents your level of discomfort after the following question: what did you feel during the treatment?.

##### Cost-efficacy

The number of expected and unexpected visits for each patient (indirect costs), the procedure performed at each session and their duration will be considered in the analysis. To calculate the direct costs, it will be computed the costs of all material used. These values will be based on the market value obtained by an average cost by three different stores of dental materials and this data will be updated during the study [20]. The duration of the treatments (time of treatment) and the cost of the materials used will be considered for the estimation of the cost-efficacy of the treatments by a ratio - cost/efficacy, being efficacy considered the pulp vitality.

##### Data analysis

The efficacy of each treatment will be assessed by five main outcomes:Success rate of pulp vitality (Primary outcome) andsurvival of restorations (secondary outcome): Kaplan-Meier survival and the Long-rank test will be used to compare the success rates between the experimental and control groups. Cox regression model with a shared frailty will be performed in order to allow the evaluation of the influence of the variables in the results.Progression of deep caries lesions (secondary outcome): Qui-square test will be used to compare this outcome between the groups.Cost-efficacy (secondary outcome): Incremental cost-efficacy ratio will be calculated considering the ratio between the total cost of each treatment and the success rate after 2 years.Self-reported discomfort (secondary outcome): Poisson regression will be used to compare both groups and to asses of the influence of other variables on this outcome.

For all analyzes, the significance value will be adjusted to 5%.

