## Abstract

**Background:**

Due to the lack of evidence to determine the best treatment for deep cavitated caries lesions in primary molars, the search for an effective restorative technique, which results in a minimal discomfort to patients, and reduce the time needed for the treatment, becomes relevant. The objective of this randomized clinical trial was to evaluate if high-viscosity glass ionomer cement (HVGIC) restorations is noninferior to restoration with calcium hydroxide cement associated with HVGIC for treatment of deep lesions in primary molars, as well as the impact of the treatments on cost and discomfort of the patient.

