**Methods:**

A non-inferiority randomized clinical trial with two parallels arms (1:1) will be conducted. Children with 4 to 8 years will be selected at Clinic of Pediatric Dentistry at Ibirapuera University. 108 teeth will be randomized into two groups: (1) Calcium hydroxide cement associated with HVGIC and (2) HVGIC restoration. Primary outcome will be considered the pulp vitality and to be evaluated after 6, 12, 18 and 24 months by two calibrated examiners. Survival of restorations will also be evaluated in the equal intervals. The duration of dentals treatment and the cost of all materials used will be considered for estimating of cost-efficacy of each treatment. Individual discomfort will be measured after each dental procedure using the Wong-Baker’s Facial Scale. For the primary outcome, Kaplan-Meier survival and the long-rank test will be used to comparison between the groups. Cox regression will be performed to assess the influence of variables on the outcome. For all analyzes, the significance level is set at 5%.

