Nevertheless, the high viscosity glass ionomer cement (HVGIC), which has been the material of choice for medium and low deep cavities in Atraumatic Restorative Treatment (ART), has not been considered in the studies that focusing in treatment of deep caries lesion [14]. Using this material in pediatric dentistry seems to be an alternative to decrease the time required for the clinical care, due to the facility to perform the restorations with HVGIC. Considering the philosophy of ART, it will be possible to restore the deep caries lesion with pulp vitality without the use of rubber dam and anesthesia. However, to date, there are no well-designed clinical trials evaluating cost-efficacy as well as other important patient-centered outcomes of the treatment of deep caries lesions with HVGIC.

Thus, this study aims as primary outcome to compare the pulp vitality of two types of treatment for deep caries lesions in primary molars (HVGIC restoration and restoration with calcium hydroxide cement associated with HVGIC) by a non-inferiority randomized clinical trial with two parallel arms. The secondary outcomes will compare the survival of restorations, caries progression, cost-efficacy and discomfort between the two treatment options. Our hypothesis is that the dental pulp vitality of teeth restored with HVGIC do not differ from teeth restored with a pulp capping material.

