### Sample size calculation and selection

Participants will be selected with ages ranging from 4 to 8 years searching for dental treatment, coming from the Clinic of Pediatric Dentistry of the Ibirapuera University, Sao Paulo, Brazil. The screening will be carried out under natural light with the aid of a wooden spatula. Children with potential for inclusion in the research will be referred for clinical examination. Children with at least one primary molar with deep cavitated caries lesion on the occlusal or occlusoproximal surfaces will be included.

Special needs patients using orthodontic appliance and / or systemic diseases that may influence the oral cavity, will be excluded. In addition, teeth with pulp exposure, spontaneous pain, mobility, abscess or fistula near the tooth, teeth with restorations, sealants or defects of enamel formation will be excluded.

Initial periapical radiography will also be performed to confirm the depth of the lesions as well as to exclude a possible pulpal involvement – presence of radiographically visible furca/periapical lesion - linked to clinical evaluation by PUFA index [15] - presence of ulceration, fistula and abscess, reported pain and pathological mobility. It will be considered as deep caries lesion those that will be located in the inner third of dentin.

To perform the sample size calculation, the expected success rates of pulp vitality using a calcium hydroxide cement as pulp capping material was considered 94% in 12–29 months [16]. It was considered that a clinically significant difference was 15% in the success rate between the groups. Therefore, considering a significance level of 0.05 and a power of 0.80, using a one-tailed test for non-inferiority studies, with a 20% increase due to a possible sample loss and 40% by cluster of more than one tooth per children, we reached the final rounded number of 54 teeth per group, resulting in 108 teeth in total [17].

Recruitment are taking place from November 2016 to April 2018. After allocation and treatment in one of the groups, with mean of 1 month per participant, these will be followed up for 24 months. Figure 1 displays the flow diagram of clinical trial’s phases.

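### The trial is designed and sized for non-inferiority, but the stated primary test is a log-rank test of equality that never uses the 15-point margin

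*Protocol article*

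**What the plan says.** **Objective and design.** The Abstract sets out to "evaluate if high-viscosity glass ionomer cement (HVGIC) restorations is noninferior to restoration with calcium hydroxide cement associated with HVGIC" and states that "A non-inferiority randomized clinical trial with two parallels arms (1:1) will be conducted". The Background section and Trial design and ethical considerations also call the trial non-inferiority.

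**Sample size** (Sample size calculation and selection). For the control, "the expected success rates of pulp vitality using a calcium hydroxide cement as pulp capping material was considered 94% in 12–29 months". Then: "It was considered that a clinically significant difference was 15% in the success rate between the groups". The level is 0.05 and the power 0.80, "using a one-tailed test for non-inferiority studies", with 20% added for loss and 40% for clustering of teeth within children. The result is 54 teeth per group.

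**Hypothesis** (end of Background): "Our hypothesis is that the dental pulp vitality of teeth restored with HVGIC do not differ from teeth restored with a pulp capping material".

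**Analysis** (Data analysis). For pulp vitality and restoration survival, "Kaplan-Meier survival and the Long-rank test will be used to compare the success rates between the experimental and control groups". The Abstract names the same test for the primary outcome. A shared-frailty Cox model is added to examine the influence of variables. On the level: "For all analyzes, the significance value will be adjusted to 5" per cent, without saying whether this is one- or two-sided.

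The 15% appears only in the sample size section.

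**The concern.** A log-rank test asks whether two survival curves are equal. Non-inferiority asks whether the new treatment is worse by less than a stated amount. Failure to reject equality is not evidence for non-inferiority, because it also occurs when there are few failures or few teeth. Rejection of equality does not rule non-inferiority out either, because a difference can be significant and still lie within the margin.

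The hypothesis is worded as no difference and the analysis section has no rule tied to 15 points. Nothing in the article as written therefore controls the chance of accepting a treatment that is worse by the margin, and that decision is the main conclusion of the trial.

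**Working it through.** **1. Reproducing the 54.** Inputs from the sample size section: control success 0.94, difference 0.15, one-sided α 0.05 (z = 1.645), power 0.80 (z = 0.842), loss 20%, clustering 40%. The article gives 94% for calcium hydroxide only. An equal true rate for HVGIC alone is inferred here.

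n = (1.645 + 0.842)² × 2 × 0.94 × 0.06 / 0.15² = 31.0 per arm

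31 / (1 − 0.20) × 1.40 = 54.25, rounded to 54. Multiplying instead, 31 × 1.2 × 1.4 = 52.1, which is close.

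Other readings do not fit:
- One-sided 0.025 needs 40 before inflation, and 64 to 70 after it.
- A difference test of 94% against 79% needs 64 (one-sided) or 81 (two-sided) before any inflation.

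So the 15% was used as a non-inferiority margin, although the article calls it a clinically significant difference.

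**2. Effective size.** 54 / 1.4 = 38.6, or about 38 teeth per arm after the plan's clustering allowance. Taking off 20% loss as well, 38.6 × 0.8 = 30.9, or about 31.

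**3. The log-rank test when HVGIC is worse by the full margin.** Assumptions: 24-month success 94% (control) and 79% (HVGIC alone), so the hazard ratio is ln 0.79 / ln 0.94 = 3.81; constant hazard per visit; visits at 6, 12, 18 and 24 months; 20% loss; clustering represented only by the smaller number of teeth. Share of simulated trials (20,000 runs per case) with a non-significant result:

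| Teeth per arm, before loss | Two-sided 5% | One-sided 5% |
|---|---|---|
| 54 | 41% | 29% |
| 38 (design effect 1.4) | 56% | 42% |

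The error implied by the sample size section is 5%.

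**4. Two possible results at 54 per arm** (two-proportion test, Wald limits).
- Control 51/54 (94.4%), HVGIC 45/54 (83.3%): difference −11.1 points, p = 0.066, so no significant difference. SE = √(0.944 × 0.056/54 + 0.833 × 0.167/54) = 0.0595. Lower 90% limit = −11.1 − 1.645 × 5.95 = −20.9 points, so non-inferiority is not shown.
- Control 54/54, HVGIC 50/54 (92.6%): difference −7.4 points, p = 0.042, so significantly different. The lower 90% limit is −13.3 points, inside the margin. The Newcombe limit is −15.5, just outside it, so the interval method matters.

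**5. A margin-based rule at 31 teeth per arm** (independent binomials, exact calculation, lower two-sided 90% limit above −15 points):

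| Interval | Power at 94% v 94% | Error at 94% v 79% |
|---|---|---|
| Wald | 82% | 7.4% |
| Newcombe | 73% | 5.5% |

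**The case against.** **The full plan may contain the rule.** This is a journal article, and a comparison of a confidence limit with the margin could be in an analysis plan that is not shown. That would excuse silence. But the article is not silent: it names the primary test twice, and the test is of the wrong kind for the stated objective.

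**The data can answer the question.** A reader might infer that the trial cannot answer its own question. The article does not support that. It plans Kaplan-Meier estimates by arm and fixes two-year success as the primary outcome, so the 24-month difference can be computed and set against 15 points. The gap is in the decision rule, not in the data. This part of the objection stands.

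**Nobody says that non-significance will count as success.** This is also right. The Abstract states the objective as non-inferiority, and no sentence says that a non-significant log-rank test will be taken to show it. That reading is an inference from the hypothesis of no difference and the lack of any other rule. The percentages in the first table are conditional on it.

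**Sidedness.** Data analysis does not state it. Two-sided is the usual form of the test, while the sample size section is one-tailed. Both are shown, and the problem remains under either.

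**The Cox model.** It can allow for clustering through the frailty term, but its stated purpose is the influence of variables and it brings in no margin.

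**Conclusion.** The point holds. The stated primary comparison does not match the non-inferiority design, the analysis as written has no rule for concluding non-inferiority, and the stated 80% power belongs to a test that the analysis section does not contain.

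If non-significance were read as support for the hypothesis, a true 15-point deficit would pass in 29% to 41% of trials at 54 teeth per arm and 42% to 56% at 38 effective teeth, where the lower figure is one-sided and the higher two-sided. These figures rest on a constant hazard, 20% loss and the plan's own clustering allowance.

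This should be corrected before analysis, because it decides the main conclusion.

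**What to change.** 1. Make the primary analysis the difference in 24-month pulp-vitality success, HVGIC alone minus control, with a confidence interval that accounts for teeth clustered within children.
2. Declare non-inferiority only if the lower limit of the two-sided 90% interval (one-sided 5%, as in the sample size section) lies above −15 percentage points.
3. Keep the log-rank test and the frailty Cox model as supportive analyses.
4. Reword the hypothesis at the end of Background: pulp-vitality success with HVGIC alone is not more than 15 points lower than with the control treatment.
5. Fix the interval method in advance and restate the power for it at about 31 effective teeth per arm. The 82% and 73% above are approximations for independent teeth. The cluster-adjusted method actually chosen needs its own figure.

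**Cost.** Changes of wording only, with no extra teeth or data. The drawback is that the restated power may fall below 80%, as it does for the Newcombe interval in the approximation above.

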## Discussion

Studies focusing in smart and comfortable techniques to children’s treatment should be conducted in order to guide the dentists to use of friendly-patient approaches. Thus, this is the first clinical trial that will evaluate as primary outcome the success rate considering the pulp vitality between restoration with calcium hydroxide cement associated with HVGIC and HVGIC restoration for treatment of deep caries lesions in primary molars in according the philosophy of ART.

The evaluation of this outcome will take into account clinical signs associated with symptoms, since that the most of the previous studies considering the survival of restoration as the primary outcome and not pondering the pulp condition. However, the main reason to use the pulp capping material is to protect the pulp tissue. Thus, it should be considered in the evaluation.

Others secondary outcomes will be considered. The choice of outcome measures was based on the efficacy of the treatment, but also in patient-centered outcomes, thinking in about the practice-based evidence where the preference of patient should be englobed in the treatment choice. Analysis of cost will be also performed in order to project the incremental cost of the treatments with higher failure rate for the public health manager.

This is important to highlighted that it will not be possible the blinding of the operators because of the evident differences between the both techniques. Nevertheless, to minimize this situation, the allocation of the treatments will be only performer after the selective caries removal. Furthermore, the patient and examiner can be considered as blinded.

Thus, our study desires to answer if it is possible to restore deep caries lesion of primary teeth only with HVGIC considering the ART philosophy. Since that this hypothesis was sustained, the pediatric dentistry can be used a friendlier technique to deep caries lesion management.

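### The ratio labelled incremental is defined as each treatment's cost over its success rate, which is an average cost-efficacy ratio and does not give the incremental cost the protocol promises

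*Protocol article*

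**What the plan says.** The definition appears in two places in the protocol article, and a third place states its purpose.

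- Data analysis: "Incremental cost-efficacy ratio will be calculated considering the ratio between the total cost of each treatment and the success rate after 2 years".
- Cost-efficacy (under Secondary outcome): treatment time and material costs feed an estimate formed "by a ratio - cost/efficacy, being efficacy considered the pulp vitality".
- Discussion: the cost analysis is meant to "project the incremental cost of the treatments with higher failure rate for the public health manager".

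The abstract also speaks of estimating cost-efficacy separately for each treatment, and its objective includes the effect of the treatments on cost.

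**The concern.** The name and the formula disagree. An incremental cost-efficacy ratio answers what one additional success costs when moving from one treatment to the other, so it needs the difference in cost and the difference in success. Cost divided by success within an arm answers another question: what each success cost on average in that arm. Neither of the two sections that define the ratio mentions a between-arm difference.

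Two things are at stake. A figure published as incremental would be read by health economists and health managers as something it is not. And two average ratios placed side by side invite a ranking. That ranking can favour a cheaper arm with clearly lower pulp survival without showing what the lost successes would have cost to keep.

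**Working it through.** **The design figures.** The article states no cost figure, so the only figure to reproduce is the sample size. It is relevant here because it shows what success difference the design expects. Inputs from Sample size calculation and selection: control success 94%; margin 15 points ("It was considered that a clinically significant difference was 15% in the success rate between the groups"); "considering a significance level of 0.05 and a power of 0.80", one-sided; 20% for loss; 40% for clustering.

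- Assuming 94% in both arms: n = 2 × 0.94 × 0.06 × (1.645 + 0.842)² / 0.15² = 31.0, so 31 per group.
- 31 / (1 − 0.20) × 1.40 = 54.25, rounded to 54 per group, 108 in total. This matches the article.

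The stated size is therefore consistent with planning for equal success.

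**The two formulas.** With C for mean cost and E for 2-year success:

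- Average ratio, as the article words it: C_HVGIC / E_HVGIC and C_control / E_control.
- Incremental ratio: (C_HVGIC − C_control) / (E_HVGIC − E_control).

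HVGIC alone has the lower average ratio exactly when C_HVGIC / C_control < E_HVGIC / E_control.

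**Illustration.** Costs are assumed, with control = 10 units. Success is 94% for control and 79% for HVGIC alone, which is the full 15-point margin.

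| HVGIC cost | Average ratio, HVGIC | Average ratio, control | Lower average ratio | Incremental ratio |
|---|---|---|---|---|
| 8 | 8/0.79 = 10.13 | 10/0.94 = 10.64 | HVGIC alone | 2/0.15 = 13.3 |
| 8.5 | 8.5/0.79 = 10.76 | 10.64 | control | 1.5/0.15 = 10.0 |
| 9 | 9/0.79 = 11.39 | 10.64 | control | 1/0.15 = 6.7 |

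The switch is at 0.79/0.94 = 84.0% of control cost.

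**Other success rates for HVGIC alone** (control 94%). The cost share below which HVGIC alone ranks better on the average ratio is:

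- 89%: 0.89/0.94 = 94.7%
- 85%: 0.85/0.94 = 90.4%
- 79%: 84.0%
- 75%, beyond the margin: 0.75/0.94 = 79.8%

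**Near equal success.** If both arms reach 94%, the incremental ratio has a zero denominator and is undefined. With about 31 effective teeth per arm, the standard error of the success difference is √(2 × 0.94 × 0.06 / 31) = 0.060, so a 95% interval is about ±12 points around the observed difference. If the design assumption is right, that interval will usually include zero. The correct ratio is then unstable and should not stand alone.

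**The case against.** The strongest defence is that this is loose wording in a condensed article, that the planned data (each arm's total cost and 2-year success) already contain everything an incremental ratio needs, and that the outcome is secondary. The second and third parts stand: nothing is lost in data collection, and the primary outcome, randomisation and sample size are untouched. The first does not. The article gives a formula, words it per treatment, and gives the same cost-over-efficacy construction in a second section. The objection here is to what is stated, not to detail left for an analysis plan.

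It may also be said that the Discussion promises an incremental cost, not an incremental ratio. That is so, but an incremental cost is still a between-arm difference, and the stated ratio does not supply one.

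Two stronger readings should be resisted.

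- A reader might infer that average ratios always favour the cheaper arm. They do not: at 8.5 v 10 with 79% v 94% success they favour control. At equal success they simply order the arms by cost, so there is no wrong ranking. Both arms receive the same HVGIC restoration and control adds a liner; nothing in the article shows how large a saving that makes.
- A reader might infer from "The number of expected and unexpected visits for each patient (indirect costs" that, because teeth are randomised, visits cannot be attributed to an arm. The same sentence goes on to include the procedure done at each session and its duration, which gives a route from visit to tooth. Any rule for sharing a visit between teeth may sit in the full protocol.

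Finally, a cheaper and less effective treatment can be a reasonable choice for a payer. That is a reason to report the incremental quantities, since they show the trade-off.

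**Conclusion.** The definition is wrong as written. The ratio named incremental is an average cost-efficacy ratio, and it does not deliver the incremental cost that the Discussion says will be projected.

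The consequence is a mislabelled result and a possible, not a certain, misleading ranking. At 94% v 79% success, HVGIC alone would look better at any cost below 84.0% of control, despite a loss of 15 points in success. Above that share the ranking goes the other way. The result rests on assumed costs, because the article gives none, and on success at the margin; the threshold moves between 79.8% and 94.7% of control cost as success with HVGIC alone moves between 75% and 89%. The point is confined to one secondary outcome.

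**What to change.** In both Cost-efficacy and Data analysis, define the ratio as (mean cost HVGIC − mean cost control) / (2-year success HVGIC − 2-year success control).

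Because the design expects nearly equal success and the denominator may be close to zero, report the cost difference and the success difference alongside the ratio, each with an interval that accounts for clustering of teeth within child. If per-arm ratios are kept as description, call them average cost-efficacy ratios and do not rank the arms by them.

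The cost is a wording change in two sections and a little more analysis of a secondary outcome. It uses costs and success rates already planned, and leaves the primary analysis and sample size as they are.

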## Methods/design

### Trial design and ethical considerations

A non-inferiority randomized, controlled, double blind (participant and examiner) clinical trial with two parallels arms (1:1) will be performed. The present protocol follows the guidelines of the Standard Protocol Items: Recommendations for Interventional Trials (SPIRIT) as detailed in online Additional file 1.

It was approved by the local ethics committee from the Faculty of Dentistry of the University Ibirapuera (registration no. 1.670.059) and was recorded in the database for registration of clinical studies (Clinicaltrials.gov registration NCT02903979).

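### Face-scale discomfort is compared by Poisson regression with no face numbering, robust variance or child clustering named, so the 5% error rate is not controlled in either direction

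*Protocol article*

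**What the plan says.** All references are to the protocol article.

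- **Self-reported discomfort:** "For this purpose, the Wong-Baker face scale [19] will be used". Immediately after treatment, "the child will point to the image which represents your level of discomfort". The section does not give the number of faces, the numbers attached to them or any cut-point.
- **Data analysis:** for this outcome, "Poisson regression will be used to compare both groups and to asses of the influence of other variables on this outcome". The closing line applies to every outcome: "For all analyzes, the significance value will be adjusted to 5" per cent. No variance estimator and no term for the child is named for the Poisson model. In the same section the Cox model is given a shared frailty.
- **Abstract, Methods:** discomfort is rated after every dental procedure.
- **Sample size calculation and selection:** 40% is added because a child may contribute more than one tooth, and "we reached the final rounded number of 54 teeth per group, resulting in 108 teeth in total". Some children should therefore give more than one rating.

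**The concern.** The response is one choice from an ordered set of pictures. Ordinary Poisson regression treats it as a count whose variance equals its mean, and a face score has no reason to obey that. If the variance exceeds the mean, the standard error is too small and the test rejects too often. If the variance is below the mean, the test rejects too rarely. Which of these applies depends partly on the labels put on the faces, and the article does not give them.

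Repeated ratings from one child are a second gap, since no term in the stated model links them.

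Discomfort is part of the trial's stated objective in the Abstract. Both the treatment comparison and the assessment of other variables on this outcome would be reported at a 5% level that the named method does not secure.

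**Working it through.** **Sample size figure.** The article plans no sample size for discomfort. Its only figure, for pulp vitality, reproduces: with 94% success in both arms, a 15-point margin, one-sided 5% and 80% power, n = (1.645 + 0.842)² × 2 × 0.94 × 0.06 / 0.15² ≈ 31 per group. Then 31 × 1.2 = 37.2, rounded up to 38, and 38 × 1.4 = 53.2, rounded up to 54. I use 54 teeth per arm below.

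**Inputs that are assumptions.** These are not in the article: six faces; codings 0–5, 0–10 in steps of 2, or 1–6; six illustrative response distributions; a two-sided test; independent teeth.

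**Dependence on numbering.** For two groups with score totals S₁ and S₂, the ordinary Poisson standard error of the log ratio of means is √(1/S₁ + 1/S₂). Multiplying all scores by k leaves the ratio unchanged and divides the standard error by √k, so z is multiplied by √k. For k = 2 the factor is 1.41: z = 1.645 (p = 0.10) becomes 2.33 (p = 0.02). This is algebra and does not depend on the assumed distributions.

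Constructed example, 54 per arm, faces from lowest to highest: control 22/13/8/5/3/3, experimental 16/13/10/7/4/4.

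- 0–5: totals 71 and 90, ratio 1.268, SE = √(1/71 + 1/90) = 0.159, z = 1.49, p = 0.135.
- 0–10: totals 142 and 180, ratio 1.268, SE = 0.112, z = 2.11, p = 0.035.
- 1–6: totals 125 and 144, ratio 1.152, SE = 0.122, z = 1.16, p = 0.247.

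The same responses give three p-values, one of them below 0.05. With a sandwich variance they are 0.234, 0.234 and 0.231. A rank test, which needs no numbering, gives 0.19.

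**False-positive rate.** In large samples the true size of the nominal 5% test is 2[1 − Φ(1.96/√(variance/mean))]. For the mostly-none distribution coded 0–5, the mean is 0.95 and the variance is 3.05 − 0.95² = 2.15. The ratio is 2.26 and the size 19%. Simulation (40,000 null trials per distribution) agrees with the formula:

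| Assumed % per face, lowest to highest | Variance/mean, 0–5 | 0–10 | 0–5 | 1–6 | Any vs none |
|---|---|---|---|---|---|
| Mostly none 60/15/10/5/5/5 | 2.26 | 35.1% | 18.8% | 5.7% | 1.0% |
| Bimodal 45/10/10/5/10/20 | 2.23 | 35.3% | 19.1% | 10.3% | 0.4% |
| Mild skew 40/25/15/10/5/5 | 1.62 | 27.8% | 12.1% | 3.9% | 0.2% |
| Uniform | 1.17 | 19.7% | 7.0% | 3.2% | 0.0% |
| Low, concentrated 50/35/10/5/0/0 | 1.01 | 16.9% | 5.0% | 0.2% | 0.5% |
| Central 5/20/30/25/15/5 | 0.64 | 8.2% | 1.3% | 0.3% | 0.0% |

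With a sandwich variance on the same data, the rate is 4.9–5.7% for every distribution and face coding, and 3.9–4.5% for the any-versus-none split.

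**The case against.** The strongest reply is that the article names only Poisson regression. It does not say that the standard errors are model-based, that raw scores are the response, or that teeth are treated as independent. Coding and variance estimator for a secondary outcome are often left to an analysis plan, which may exist. Poisson regression with a robust variance is workable here, and on a dichotomised rating it would estimate a ratio of proportions. This limits the point: if an unseen plan specifies a robust variance, most of the error-rate problem disappears. But the choice of model is stated, it is a count model for an ordered category, and as written it does not secure 5%. The same section does find room for a frailty term in the Cox model.

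A reader might infer three stronger things that the article does not support.

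- **That false positives will be several times 5%.** This holds only for some combinations, mainly 0–10 coding. Centrally clustered scores, most 1–6 codings and a dichotomised rating give rates below 5%.
- **That the scoring could be chosen to produce a result.** The article cites a source for the scale. Whether that source fixes the numbering cannot be checked here.
- **That the Discussion's hope for a more child-friendly technique rests on this test.** The Discussion ties it to the trial hypothesis being sustained, and the Background states that hypothesis as pulp vitality.

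On clustering, the size and direction of the effect are unknown. Teeth are randomised individually, so one child may have teeth in both arms, and ignoring the child need not inflate the error of the treatment comparison.

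**Conclusion.** The point stands as one of uncontrolled error, not certain inflation. That the p-value depends on the numbering is an algebraic property of ordinary Poisson standard errors. The size of the error rests on the assumed faces, codings and distributions, and runs from well under 1% to about 35% against a nominal 5%. The lack of a child-level term is a further gap that I have not quantified. Only the secondary discomfort comparison and its covariate assessments are touched. The non-inferiority comparison of pulp vitality and the 54 teeth per group are not.

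**What to change.** State in advance how the faces are coded, and replace the Poisson sentence with one of these:

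- a proportional-odds model with arm and cavity type as covariates and standard errors clustered on the child; or
- Poisson regression with a sandwich variance clustered on the child, reporting the ratio of means, or the ratio of proportions if the rating is dichotomised at a pre-stated cut-point.

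The coding still has to be stated under the second option. A sandwich variance removes the effect of multiplying the scores but not of shifting them (0.234 against 0.231 in the example). The first option uses only the order of the faces, at the price of assuming a common odds ratio across them.

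The cost is one changed sentence. No new data are needed and the software is standard. In some cases the p-value will be less favourable: in the 0–10 example it moves from 0.035 to 0.234.
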